### Statistical analyses and power

This estimated sample size for the main outcome measures of physical performance was based on an assumed correlation of 0.7 between the pre- and post-intervention outcome measures, and an effect size of Cohen’s *d* = 1.2 for gait speed based on data from Román et al. [29] that examined the effects of a multi-strain probiotic on gait speed and the TUG test in a study cohort of 35 (17 and 18 in treatment and placebo groups, respectively). To have a power of 80% and a significance level of 5%, our study aims to enrol an estimated sample size of 74 participants (37 per group), taking into account a conservative ~ 30% dropout rate.

The study hypotheses will be addressed using a hierarchical linear model analysis to test for significant differences between the two comparative groups (intervention and placebo) over time. A primary intention to treat (ITT) analysis will be conducted on all the participants who complete the trial. Additionally, a secondary analysis will be carried out to include only participants who consumed ≥ 90% of their supplement over the course of the intervention period. Between-group comparisons will be made using linear models and statistical significance set at *p* < 0.05. Where there are significant group xtime interactions, planned contrasts will compare changes from baseline under each intervention. Similar tests will be performed for the secondary hypotheses, using appropriate transformations if these measures exhibit non-normal distributions across time points. This analysis will allow for the control of any baseline group differences and to test for moderation effects in terms of these variables over time. Analysis of microbial community composition will be conducted using Phyloseq and vegan package in R version 3.6.1 as per protocol.

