### Participant withdrawal and/or discontinuation from the study

Participants will be informed they may withdraw from the study at any time. This will be explained during the consent process and is detailed in the ICF. Participants will be made aware they may be discontinued at any time at the discretion of the investigators for safety reasons, or the inability of the participant to comply with the protocol-required schedule of study visits or procedures. Investigators may discontinue or withdraw a participant from the study for the following reasons:Non-compliance to study protocol.Occurrence of AE related to the intervention, laboratory abnormality, or other medical condition such that participation in the study would not be in the best interest of the participant. This includes whether the participant meets an exclusion criterion (newly developed or not previously recognized).Disease progression requiring discontinuation of the study intervention.

Throughout the duration of the study, the research team will evaluate the well-being of all participants. If continued participation is considered harmful to an individual’s health or safety, that participant will be withdrawn from the study. If a participant is discontinued or withdraws from the study, every attempt will be made to have them complete an Early Termination Visit to determine the participant outcome, to ensure they are withdrawn safely, and to close off any unresolved AEs, if possible. Participants who withdraw after randomization will not be replaced.

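### The primary analysis is called intention to treat but is limited to participants who complete the trial, so it is a completer analysis

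*Protocol article*

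**What the plan says.** Statistical analyses and power defines the primary population in one sentence: "A primary intention to treat (ITT) analysis will be conducted on all the participants who complete the trial". The only other efficacy population named there is adherence-based: "a secondary analysis will be carried out to include only participants who consumed ≥ 90% of their supplement over the course of the intervention period". The same section sets the target, "our study aims to enrol an estimated sample size of 74 participants (37 per group"), and describes it as "taking into account a conservative ~ 30% dropout rate". The planned analysis is a hierarchical linear model comparing the groups over time, and mixed models are to include the subject as a random factor.

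The Abstract gives the primary outcome as the between-group change from baseline to week 16. Study duration has participants continuing to a follow-up visit at week 20. Study assessments schedules the performance tests at baseline and weeks 8, 16 and 20.

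The section on withdrawal and discontinuation says: "Investigators may discontinue or withdraw a participant from the study for the following reasons:Non-compliance to study protocol". It lists intervention-related adverse events among the further reasons. Those who withdraw after randomisation are not replaced, and for anyone who leaves, "every attempt will be made to have them complete an Early Termination Visit".

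**The concern.** The label and the rule cannot both be true. Random assignment makes the two arms comparable as randomised. Completing the trial happens after randomisation and may be affected by the assigned product, so comparing completers only is no longer protected by the randomisation.

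The document shows ways in which completion could be related to treatment. Investigators may withdraw people for non-compliance or for adverse events related to the intervention. The Risk–benefit analysis section lists gastrointestinal side effects for probiotics and prebiotics, and the placebo is maltodextrin. These are possibilities, not evidence that dropout will differ between the arms.

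At stake is the headline result for every primary outcome. Readers would be told that it is intention to treat when it is not. Neither named population keeps everyone randomised, so the plan as written offers no analysis against which the completer result could be checked.

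**Working it through.** **Inputs from the article.** 74 randomised, 37 per arm, 1:1; dropout about 30%; primary endpoint at week 16; last visit at week 20; d = 1.2 for gait speed; pre-post correlation 0.7; 80% power; 5% significance (taken as two-sided, which is not stated).

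**The plan's own figure.** I could not reproduce 74 from these inputs. Using the t-based two-sample calculation, then dividing by 1 − 0.30 and rounding up:
- Post-only, SD 1: 12 per arm; 12/0.7 = 17.1, so 18; total 36.
- Change score, SD √(2(1 − 0.7)) = 0.775: 8 per arm; 8/0.7 = 11.4, so 12; total 24.
- Baseline-adjusted, SD √(1 − 0.7²) = 0.714: 7 per arm; 7/0.7 = 10; total 20.

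That mismatch is a separate matter. It neither supports nor weakens this point, which uses only the 74 and the 30%.

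**How many the rule excludes at the planned rate.**
- 74 × 0.30 = 22.2, about 22 excluded.
- 74 × 0.70 = 51.8, about 52 analysed.
- 37 × 0.70 = 25.9, about 26 per arm.

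**Power.** With 26 per arm and d = 1.2 on the post-only SD, power is about 99%. On the plan's own effect size the harm is therefore possible bias and a wrong label, not lost power.

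**Week 16 and week 20.** If completing the trial means finishing scheduled participation, it means attending week 20. A participant seen at weeks 8 and 16 but not at week 20 has full primary-endpoint data and still falls outside the set.

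**Size of bias (illustration by assumption; the article gives no dropout by arm).** Let p be the dropout proportion in an arm, and let D be the amount, in SD, by which dropouts' outcomes would fall below those of completers. Within an arm, the mean of all randomised equals the completer mean minus p × D. Hence

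bias (completer difference minus all-randomised difference) = p_syn × D_syn − p_pla × D_pla.

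With the same D in both arms this becomes D × (p_syn − p_pla):

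| Dropout, synbiotic v placebo | D = 0.2 | D = 0.5 | D = 1.0 |
|---|---|---|---|
| 30% v 30% | 0 | 0 | 0 |
| 35% v 25% | 0.02 | 0.05 | 0.10 |
| 40% v 20% | 0.04 | 0.10 | 0.20 |

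All rows average 30% dropout. Swapping the arms reverses the sign. Equal dropout rates can still bias the result if D differs by arm, because the formula then gives 0.30 × (D_syn − D_pla).

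**Is the restriction needed?** No. A likelihood-based hierarchical model does not need complete records. Baseline data, and week-8 data from those who leave later, can enter it.

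**The case against.** The most charitable reading is that the sentence means analysis regardless of adherence, in contrast to the 90% set that follows. That may be what was intended, but the sentence still does not make the set all-randomised. A statistical analysis plan may say more. However, this is a stated population and not an omitted detail, so a later document could cure it only by contradicting the sentence. It could settle what completion means, and the week-20 point depends on that.

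Several stronger readings are tempting, and the documents do not support them:
- **That 30% of participants will be lost.** The 30% is a planning allowance that the article itself calls conservative. Actual loss is unknown.
- **That the effect will be overstated.** Suppose synbiotic dropouts would do 0.5 SD worse than completers and placebo dropouts no worse. The formula then gives 0.30 × 0.5 = 0.15 SD in favour of the product. Nothing in the article supports that one-arm pattern. It describes side effects as usually minor, and no bias or understatement is equally open.
- **That early-termination efficacy data are thrown away.** The visit is attempted, and its stated purposes are participant outcome, safe withdrawal and adverse-event closure. Performance tests are not mentioned.
- **That the primary set is nearly the 90% adherence set.** Withdrawal for non-compliance is permitted, not automatic. A participant with low adherence who finishes stays in the primary set and leaves only the secondary one.

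It is also fair to say that a mixed model would not remove all of the bias. Someone who leaves before week 8 may contribute a baseline value only.

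**Conclusion.** The concern holds as a contradiction in the sentence that defines the primary population: what is labelled intention to treat is a completer analysis. At the planned dropout rate it would leave out about 22 of 74 randomised participants, and possibly some who have week-16 data.

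Bias is possible, and its size and direction are unknown. In the illustration it is zero at equal dropout and up to 0.20 SD either way at 40% v 20%. Those figures rest on assumed dropout rates by arm and an assumed outcome gap common to both arms, and they are not estimates for this trial. They also do not measure what the rewording would recover, because the mixed model corrects only as far as the observed data predict the missing outcomes.

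The sentence should be corrected because it governs every primary result and the correction is cheap.

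**What to change.** Replace the sentence with:

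> The primary analysis includes all randomised participants in their assigned arm, using every available visit in the planned likelihood-based mixed model under a missing-at-random assumption, with a sensitivity analysis for data missing not at random.

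Keep the completer analysis if wanted, but label it supportive and say which visit defines completion. The withdrawal rules need no change to cure this contradiction.

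The cost is a wording change and one sensitivity analysis, with no extra participants, visits or procedures. The rewording does not recover outcomes that were never measured, which is why the sensitivity analysis belongs with it.

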**Methods:**

Seventy-four elderly (60–85 years) participants will be randomized in a double-blind, placebo-controlled fashion to either an intervention or control group. The intervention group (*n* = 37) will receive oral synbiotic formulation daily for 16 weeks. The control group (*n* = 37) will receive placebo. Assessments of physical performance (including Short Physical Performance Battery, handgrip strength and timed up-and-go tests) and muscle ultrasonography will be performed at 4 time points (baseline and weeks 8, 16 and 20). Likewise, body composition via bioelectric impedance analysis and blood and stool samples will be collected at each time point. Dual-energy X-ray absorptiometry will be performed at baseline and week 16. The primary outcomes will be between-group changes in physical performance from baseline to 16 weeks. Secondary outcomes include changes in body composition, muscle mass and architecture, fecal microbiota composition and diversity, and fecal and plasma metabolomics.

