### Hypotheses and study endpoints

#### Primary aims

We hypothesize 16 weeks of ingesting a synbiotic preparation compared to placebo will result in statistically significant improvements (within-group and between-group) in:4-m gait speedStanding balanceRepeated chair risesTimed up and go Handgrip strength

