Wilcoxon’s signed-rank test, Spearman’s rank correlation (p), Pearson’s correlation (r), multiple linear regression, and/or linear mixed models will be used to examine associations and appropriate comparisons depending on the distributions of the variables. Relationships between markers of functional performance, ordinations of stool microbiota composition, and stool/plasma metabolites will also be assessed using the Structural Equation Model to enable causal assumptions to be interpreted between variables to ensure these relationships are not “coincidental” and linear mixed models. All mixed models will include the subject as a random factor and time as a continuous covariate. Backward stepwise regression will be used to identify the strongest predictors of changes in aspects of functional performance. The false discovery rate for all tests will be controlled by adjusting *P* values using the Benjamini–Hochberg procedure. Adjusted *P* values will be presented as *Q* values. Statistical analyses will be completed using SPSS v.26. 11.2.2

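### The primary outcome is the between-group change to week 16, but the statistical section names no test of that difference; the interaction it tests is not specific to week 16, and the hypotheses add within-group significance

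*Protocol article*

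**What the plan says.** All references are to the protocol article.

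- **Abstract, Methods:** "The primary outcomes will be between-group changes in physical performance from baseline to 16 weeks". Study design calls the trial a placebo-controlled superiority study.
- **Hypotheses and study endpoints, Primary aims:** the synbiotic, compared with placebo, "will result in statistically significant improvements (within-group and between-group) in" five measures. The Secondary aims use the same form of words.
- **Statistical analyses and power, primary model:** a hierarchical linear model is used "to test for significant differences between the two comparative groups (intervention and placebo) over time". A later sentence says "Between-group comparisons will be made using linear models and statistical significance set at" the 5% level. Neither sentence names a visit.
- **Same section, contrasts:** "Where there are significant group xtime interactions", "planned contrasts will compare changes from baseline under each intervention".
- **Same section, coding of time:** "All mixed models will include the subject as a random factor and time as a continuous covariate".
- **Same section, other methods:** the signed-rank test, a paired method, appears in a list of methods for associations and comparisons. It is tied to no outcome.
- **Study assessments and Study duration:** visits are at baseline and weeks 8, 16 and 20. Product stops at week 16.

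**The concern.** The definition of the primary outcome and the analysis do not meet. The abstract asks one question: do the arms differ in change at week 16? The statistical section offers a difference over time at no named visit, an interaction in continuous time across a period that includes four weeks off product, and follow-up contrasts that appear to look at each arm separately.

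Two things are at stake. First, a real week-16 effect that fades after the product stops could be missed by the interaction, and an effect absent at week 16 could be picked up by it. Second, the hypotheses make within-group improvement part of the efficacy statement. A within-arm change mixes any product effect with practice on repeated tests, regression to the mean, and the avoidance of fermented foods that the inclusion criteria require of both arms. Significance in one arm and not in the other is not evidence that the arms differ.

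**Working it through.** The plan gives no power or error rate for the interaction or for any contrast, so there is no figure of its own to reproduce here.

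**Inputs from the article.** 37 per arm with about 30% dropout gives 37 × 0.7 = 25.9, so 26 per arm. Pre-post correlation is 0.7. The level is 5%, taken as two-sided. Visits are at weeks 0, 8, 16 and 20.

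**Assumptions.** The correlation of 0.7 holds between every pair of visits (compound symmetry). Time enters linearly. The week-16 effect is 0.612 baseline SD, close to what 26 per arm can detect with 80% power on change scores. Half of it has been reached by week 8.

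**Week-16 contrast.** The standard error of the difference in change is √[(2/26) × 2 × (1 − 0.7)] = 0.215 SD. Then z = 0.612/0.215 = 2.85, and power is Φ(2.85 − 1.96) = 81%.

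**Linear interaction.** Mean visit time is 11 weeks. The deviations are −11, −3, 5 and 9, with squares summing to 236. The standard error of the slope difference is √[(2/26) × 0.3/236] = 0.00989 SD per week. If δ is the between-group effect at each visit and c the deviation, z = Σcδ/(236 × 0.00989) = Σcδ/2.334.

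| Effect at weeks 8, 16, 20 (SD) | Σcδ | z | Interaction significant | Week-16 contrast significant |
|---|---|---|---|---|
| 0.306, 0.612, 0.306 (half lost) | 4.896 | 2.10 | 55% | 81% |
| 0.306, 0.612, 0 (all lost) | 2.142 | 0.92 | 15% | 81% |
| 0.306, 0.612, 0.612 (kept) | 7.650 | 3.28 | 91% | 81% |
| 0, 0, 0.612 (week 20 only) | 5.508 | 2.36 | 66% | 5% |

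Using the t distribution with 50 degrees of freedom lowers these powers by less than 2 percentage points. A simulation at 0.6 SD agrees: 14% against 78% (all lost), 88% against 78% (kept), 62% against 5% (week 20 only). If visit were categorical instead, the 3-degree-of-freedom interaction would have 66% power in the half-lost case, still below 81%.

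**At the plan's own effect size.** Taking d = 1.2 as baseline SDs multiplies each z by 1.2/0.612 = 1.96. The half-lost case then has z = 4.11 and 98% power. The all-lost case has z = 1.80 and 44% power, against more than 99% for the week-16 contrast.

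**Within-arm reading.** Suppose there is no true difference and both arms change by the same amount. The article gives no figure for a shared change, so 0.2 to 0.6 SD of the change score is assumed. One-sample t-test power w at n = 26, and the chance w(1 − w) that the synbiotic arm is significant and the placebo arm is not:

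| Shared change (SD of change) | w | w(1 − w) |
|---|---|---|
| 0.2 | 0.165 | 14% |
| 0.3 | 0.313 | 21% |
| 0.4 | 0.500 | 25% |
| 0.5 | 0.688 | 21% |
| 0.6 | 0.836 | 14% |

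**Same question with the interaction required first.** In simulation with a shared change of 0 to 0.5 baseline SD and 26 per arm, a significant interaction followed by significant synbiotic-arm improvement at week 16 occurred in 0.4% to 4.1% of runs. The direct week-16 contrast was significant in 4.7% to 5.3%.

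**The case against.** The best reply is that the between-group analysis is explicit and comes first. The model is built to test differences between arms, between-group comparisons are planned without any condition, the abstract fixes the comparison and the visit, and the interaction is itself a between-group test. All of that stands. A reader might infer that the trial could declare efficacy from improvement in the synbiotic arm alone. The documents do not support that. If both arms improve equally, the interaction fails about 95% of the time and no planned contrast follows. The 14% to 25% above is therefore not the error rate of the written plan. It applies only if the within-group hypotheses are read on their own.

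The contrast sentence can also be read as comparing the change under synbiotic with the change under placebo. That is possible, but the contrast would still have no named visit and would appear only after a significant interaction. Likewise, requiring within-group and between-group significance together would be stricter than a between-group claim, not looser. The text does not say whether both are needed.

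The signed-rank test is assigned to no primary outcome, so little should be built on it.

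Finally, a condensed article may leave model detail to a fuller document. But here the article itself states the hypotheses, the condition for the contrasts and the coding of time, and together these do not test what its abstract defines. The sentence on continuous time sits among the association analyses, yet it covers all mixed models, and a hierarchical linear model is one.

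**Conclusion.** The point holds in limited form and should be fixed. No stated test targets the between-group difference at week 16 that defines the primary outcomes, and the within-group wording in the hypotheses leaves room for a reading that a placebo-controlled superiority trial should exclude. The gated route does not inflate false positives.

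The main cost is a mismatch between test and question. At 0.61 SD the linear interaction has about 55% power (half the effect lost by week 20) or 15% (all lost) where the week-16 contrast has 81%, and it is significant about 66% of the time for an effect seen only at week 20. The mismatch does not always cost power: if the effect persists to week 20 the interaction has more, and at d = 1.2 the half-lost case costs almost nothing. The figures rest on compound symmetry, linear time, 26 per arm and assumed effect profiles. The article gives no information on persistence after the product stops.

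**What to change.** 1. In the statistical section, name the between-group difference in change from baseline to week 16, with 95% confidence interval, as the deciding contrast for each primary outcome. Estimate it from the longitudinal model with visit as a categorical factor, and report it whatever the interaction p-value.
2. Remove within-group significance from the primary and secondary efficacy hypotheses. Report within-arm changes descriptively, without using them to judge efficacy.
3. State that the signed-rank test is not evidence of efficacy. For non-normal outcomes, use a between-group method.
4. Keep week 20 as a separate, named follow-up comparison.

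This changes wording and model specification only. It needs no extra participants, visits or measurements, and should be recorded before unblinding.

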#### Study intervention

All eligible participants will be randomized equally (1:1) into either treatment (synbiotic) or control (placebo) groups. The study treatment will consist of a multi-strain synbiotic (SYN) powder containing inulin and a combination of probiotic strains. Placebo (PLA) will consist of maltodextrin, which will match synbiotic in appearance, taste, and consistency. Both SYN and PLA sachets will be 1800 mg. The participants will be instructed to consume 1 sachet daily (orally, dissolved in water, and at the same time each day) for the entire intervention period. Both SYN and matching PLA will be provided by Lallemand Health Solutions (Montreal, QC, Canada). Enrolled participants will be asked to make no changes to their current exercise habits or usual dietary intakes and abstain from taking any dietary supplements containing prebiotics and/or probiotics during the study. A list of prohibited medications is provided in Supplementary File 1.

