### Randomization and masking

Participants who fulfil the eligibility criteria and consent to participate will be randomly assigned (1:1) to receive either a synbiotic (intervention) or placebo (control). Randomization will be completed by an independent (unblinded) third party using a random number generator in Microsoft Excel. To perform random allocation, stratified block randomization will be used. The unblinded staff will have no interaction with study participants and will not be involved in the collection or analysis of data. They will assign each participant to one of two intervention groups (synbiotic or placebo) and allocate IP based on stratification factors consisting of gender, age, and handgrip strength (“normal” or “low”, based on EWGSOP2 criteria [8]; men: “normal” ≥ 27kg or “low” < 27 kg and women: “normal” ≥ 16kg or “low” < 16 kg). Stratification data will be collected by blinded study investigators from each participant during their screening visit and will be submitted to the unblinded staff responsible for group allocations.

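### The plan ties adjustment to unspecified baseline group differences instead of naming the baseline outcome and the stratification factors, which leaves covariate choice open and, on the natural reading of the model, costs about 15% in variance

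*Protocol article*

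**What the plan says.** Under *Randomization and masking*, the protocol article states that "stratified block randomization will be used" and that unblinded staff will "allocate IP based on stratification factors consisting of gender, age, and handgrip strength". Handgrip is split into normal and low by sex-specific cut-offs. Handgrip strength is also a primary outcome.

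Under *Statistical analyses and power*, the hypotheses are to be tested by a "hierarchical linear model analysis to test for significant differences between the two comparative groups (intervention and placebo) over time". The follow-on step is "Where there are significant group xtime interactions, planned contrasts will compare changes from baseline under each intervention". Between-group comparisons by linear models are also planned, without named covariates. The statement on covariates is "This analysis will allow for the control of any baseline group differences"; the same sentence goes on to promise moderation tests on those variables. The variables meant are not listed. The next paragraph, mostly about associations, adds: "All mixed models will include the subject as a random factor and time as a continuous covariate". None of these sentences mentions gender, age or handgrip category as a model term.

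**The concern.** Two things are fixed badly.

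- **Basis of adjustment.** In a randomised trial, covariates should be chosen in advance because they predict the outcome or were used in the allocation. The text refers instead to baseline differences between the groups, of any kind, with no list. An analyst could add whichever covariates look unbalanced once the data are in. With five primary hypotheses and 74 participants, different covariate sets can move individual results across the significance line.
- **Use of the baseline outcome.** A group-by-time contrast with a free baseline mean in each arm subtracts the baseline value in full. Randomisation makes the baseline means equal in expectation, and using that fact gives a more precise estimate from the same participants.

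**Working it through.** **Inputs from the protocol article.** The pre-post correlation is r = 0.7, with 37 per group and about 30% dropout (*Statistical analyses and power*). Completers per arm: 37 × 0.70 = 25.9, taken as 26. The outcome SD is set to 1.

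**The plan's own figure.** The plan gives no precision figure for this point; its only related figure is the total of 74. That does not reproduce from d = 1.2, 80% power and two-sided 5%. An analysis of the final value only needs 12 per arm, so 24/0.70, or 35 in total. Using the correlation lowers it further. This is a separate matter and does not affect what follows.

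**Step 1: baseline handling at week 16.** The variance of the between-arm contrast is 2v/n, where v depends on the method.

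- Change score: v = 2(1 − r) = 2 × 0.3 = 0.60; SE = √(2 × 0.60/26) = 0.215.
- Baseline-adjusted: v = 1 − r² = 1 − 0.49 = 0.51; SE = √(2 × 0.51/26) = 0.198.
- Variance ratio: 0.51/0.60 = 0.85, a 15% reduction.
- Equivalent sample: 0.60/0.51 = 1.176, about 18% more participants; 0.176 × 52 completers ≈ 9.
- Detectable effect at 80% power, two-sided 5%, t with 50 degrees of freedom: 0.61 SD against 0.57 SD.

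**Step 2: does this carry over to the repeated-measures model?** Generalised least squares for a random-intercept model (correlation 0.7 between all visits, 26 per arm, complete data), with linear time scaled to 16 weeks:

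| Visits (weeks) | SE, free baseline means | SE, equal baseline means | Variance ratio |
|---|---|---|---|
| 0, 16 | 0.215 | 0.198 | 0.85 |
| 0, 8, 16 | 0.215 | 0.197 | 0.84 |
| 0, 8, 16, 20 | 0.158 | 0.145 | 0.83 |

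With categorical time, the week-16 contrast gives 0.215 against 0.198 (ratio 0.85) for all three visit sets. The gain is therefore 15 to 17% whichever way time is coded.

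**Step 3: adding the stratification factors as main effects.** The share of outcome variance they explain (R²) is not in the document; 0.1, 0.3 and 0.5 are assumptions. Simulation with 26 completers per arm at weeks 0, 8 and 16 gave:

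| Model | Variance ratio, with / without factors (R² = 0.1, 0.3, 0.5) |
|---|---|
| Random intercept, group-by-time | 1.00, 1.00, 1.00 |
| Week-16 linear model, baseline outcome included | 0.98, 0.94, 0.84 |
| Week-16 linear model, no baseline outcome | 0.88, 0.73, 0.50 |

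The first row is 1.00 because the factors do not change within a participant. With complete data the group-by-time contrast uses only within-participant differences, so neither the estimate nor its standard error moves.

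**The case against.** **The stratification factors may simply be in the analysis plan.** Listing fixed-effect covariates is routine content of a statistical analysis plan, none is shown here, and this is a condensed article. That stands as far as the bare omission goes. It does not excuse the sentence on baseline differences, which is stated text and gives a poor basis for adjustment.

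**The sentence may be harmless.** It says what the model can do and contains no instruction to select covariates by observed imbalance. It could also mean that the repeated-measures model deals with baseline outcome values. Both readings are fair: data-driven selection is permitted by the text, not prescribed. If baseline outcome values are meant, the sentence still does not settle whether they are subtracted, adjusted for or constrained, and Step 1 shows that this matters.

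**Free baseline means are nowhere stated.** Correct. They are inferred from the interaction test and the reference to changes from baseline, so the 15% is conditional on that reading.

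**Stronger readings that the document does not support:**

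- A reader might infer that the models contain only subject and time. The text says these are included, not that nothing else is, and the section also specifies group and group-by-time terms.
- A reader might infer that ignoring the stratification loses precision in the primary test. With complete data it does not (ratio 1.00).
- A reader might quote large effects of omitting the factors: confidence intervals that could be 11%, 16% or 29% narrower, and a true type I error of about 2.8%, 1.9% or 0.6%, at R² of 0.2, 0.3 or 0.5. These need assumed R² values, balance within strata and a between-group model without baseline, which the plan does not state. The error would also be conservative.

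At the plan's own d = 1.2, power with 26 completers per arm is 99% or more in every version, so the gain matters only if the true effect is smaller.

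**Conclusion.** The point holds in a limited form. The randomisation uses three factors that no stated model names, and the only statement on adjustment is open-ended, so covariate choice is not fixed before the data are seen. On the natural reading of the group-by-time model, the primary contrast gives up about 15% of variance (15 to 17% across visit sets) that baseline adjustment or equal baseline means would recover: SE 0.215 to 0.198 SD at week 16, worth about 18% more participants. This rests on r = 0.7 from the plan, 26 completers per arm, equal correlation between visits and free baseline means. Naming the stratification factors is good practice because it matches the analysis to the design and closes the covariate choice. Its precision gain is confined to the separate between-group linear models, where the variance ratio with baseline included is 0.98, 0.94 or 0.84 at assumed R² of 0.1, 0.3 or 0.5. This should be corrected, but it does not invalidate the primary test.

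**What to change.** Replace the sentence on control of baseline differences, before unblinding, by: *All between-group models adjust for the baseline value of the outcome (or constrain baseline means to be equal across arms) and include gender, age and handgrip category as used in randomisation as fixed effects; no covariates are added because of observed imbalance.* Any moderation test should name its variables in the same place.

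The cost is wording and about three degrees of freedom. No change to data collection or sample size is needed.
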